**Methods:**

In total, 50 RA patients with moderate disease activity are randomized to receive initially either a portfolio diet based on several food items with suggested anti-inflammatory effects or a control diet during 2 × 10 weeks with 3 months wash-out between diets. Food bags are delivered weekly by a home food delivery chain and referred to as the fiber bag and the protein bag, respectively, to partially blind participants. Both groups continue with regular pharmacological treatment. Known food biomarkers will be analyzed to measure intervention compliance. Impact on disease severity (measured by DAS28, a composite score which predicts disability and progression of RA), risk markers for cardiovascular disease and quality of life are evaluated after each diet regimen. Metabolomics will be used to evaluate the potential to predict responders to dietary treatment. A health economic evaluation is also included.

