### Research objective and specific questions

We hypothesize that an anti-inflammatory diet, in addition to pharmacological treatment, can improve health and quality of life in patients with rheumatoid arthritis. Specific questions are if an anti-inflammatory diet, compared to a usual Swedish diet, can reduce inflammation, pain and disease activity; reduce risk markers of cardiovascular disease; improve body composition; improve quality of life; reduce patient and societal costs related to the disease, and if metabolomics can be used to predict responders.

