### Analysis of outcome

Outcomes are measured after each diet regimen. Primary outcome is DAS28, where we expect a difference between diet regimens > 0.6 units (considered clinically relevant) in the intention-to-treat analysis. Secondary outcomes include DAS28-CRP (where hs-CRP is used instead of ESR in the DAS28 calculation), inflammation markers, anthropometry, QoL, HAQ, blood lipids, blood pressure, acute health care visits and NSAID and corticosteroid consumption. Differences in outcomes will be compared for the two diet regimens in ANCOVA analyses, adjusting for baseline disease activity scores and potential confounders (e.g., age, other lifestyle factors). Mixed models also will be applied to fully handle missing data. Interaction by sex and socio-economic position will be evaluated.

Drop-outs will be included in secondary analyses of changes in DAS28 within one diet period if they have completed at least one diet period. Drop-out analyses will be carried out in that baseline information will be compared between drop-outs and those who complete the study.

Data will be entered and stored at the Dept Internal Medicine and Clinical Nutrition, Sahlgrenska Academy, University of Gothenburg, Sweden. Stored data files will not contain any personal identifying information; only the PI will have the code list and this will be kept in a locked drawer. Quality control procedures of data will be carried out by the PI. All members of the research team have access to final trial dataset. Results will be published in international peer-reviewed journals. They will also be shared with professional societies in rheumatology and nutrition. Participants will receive information about their own results at the end of the trial.

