### Sample size

To detect a DAS28 difference of 0.6 units (clinically relevant) with 90% power and α = 0.05, 38 patients are needed in cross-over design. Skoldstam [13] detected a difference of 0.6 units with 30 patients per group in a diet parallel trial. We have carried out a pilot cross-over diet study that detected a difference of 0.34 units with 23 patients, confirming that cross-over design reduces the sample size (unpublished results). To account for drop-out or non-compliance, ADIRA cross-over study included 50 women and men.

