### Metabolomics

For metabolomics, serum samples will be analyzed with nuclear magnetic resonance (NMR) at the Swedish NMR Centre at University of Gothenburg, Sweden, as well as with mass spectrometry (MS) at Chalmers Technical Institute, Gothenburg, Sweden. We will use an untargeted metabolomics approach for a global description of the metabolites that can be found in participants’ serum using unsupervised statistical analyses, ie principal component analysis (PCA). Subsequently supervised clustering, ie orthogonal projection to latent structures-discriminant analyses (OPLS-DA [25]) and OPLS-EP [26] (for paired data) will be performed to compare metabolites between patients who respond and who don’t respond to the inflammatory diet. Finally, in a targeted metabolomics approach, metabolites providing the greatest discrimination between groups of responders vs. non-responders will be identified using publicly and commercially available as well as in-house developed databases.

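### The metabolomics model and metabolite shortlist rest on a responder/non-responder label; a model of the graded response would probably get more from the same samples

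*Protocol article*

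**What the plan says.** The aim appears twice in the protocol article. The abstract states: "Metabolomics will be used to evaluate the potential to predict responders to dietary treatment". The research objective asks "if metabolomics can be used to predict responders".

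The Metabolomics section starts with an unsupervised PCA and then names the supervised methods: "orthogonal projection to latent structures-discriminant analyses (OPLS-DA [25]) and OPLS-EP [26] (for paired data"). These "will be performed to compare metabolites between patients who respond and who don’t respond to the inflammatory diet" (the anti-inflammatory diet is evidently meant). In the last step, "metabolites providing the greatest discrimination between groups of responders vs. non-responders will be identified". So both the supervised model and the selection rule are tied to two classes.

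The section gives no response measure, cut-off, expected responder share or error level. The Analysis of outcome section states: "Primary outcome is DAS28, where we expect a difference between diet regimens > 0.6 units (considered clinically relevant"). There DAS28 is analysed as a continuous score by ANCOVA and mixed models. The Sample size section says "38 patients are needed in cross-over design" and that the "ADIRA cross-over study included 50 women and men".

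**The concern.** If response is a change in a continuous score, a class label treats a marginal and a large improvement alike, and treats two patients just either side of the cut as opposites. The Limitations section itself says that disease activity in RA varies over time and that DAS28 is partly subjective, so some labels near a cut would reflect fluctuation. No clinical or regulatory reason for a cut is given.

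The sample is small for an untargeted panel. With 38 patients and 30% responders, the smaller class has about 11 people (38 × 0.30 = 11.4). What is at stake is how many true predictors are found, and how much noise enters the list sent on for targeted identification.

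**Working it through.** **The plan's own figure.** The article gives no power figure for the metabolomics analysis. Its only sample-size figure, 38 for the primary comparison, comes without an SD. Back-solving n = (SD × (z₀.₉₇₅ + z₀.₉₀) / 0.6)² gives SD = 0.6 × √38 / (1.960 + 1.282) = 1.14 for within-patient differences, taking alpha as two-sided. This neither confirms nor refutes the 38. It is used here only for the lower n and to illustrate responder shares.

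**Inputs**
- n = 38 and 50 (Sample size section).
- Correlation r between a metabolite and the response: 0.3 to 0.5, wider 0.2 to 0.6. Assumed.
- Responder share: 30 to 50%, wider down to 20%. Assumed. As an illustration only, if 0.6 were an individual cut on the between-diet difference with SD 1.14, a mean of 0.6 gives 50% responders, the pilot's 0.34 gives Φ(−0.26/1.14) = 41%, and a mean of zero gives Φ(−0.6/1.14) = 30%.
- Two-sided 0.05 per metabolite, unadjusted. Assumed.

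**Step 1: attenuation.** Under bivariate normality, cutting the response at the point c that leaves a share p of responders multiplies r by φ(c)/√(p(1−p)). The squared factor is the asymptotic efficiency.
- p = 50%: 0.3989/0.5 = 0.798; efficiency 0.64.
- p = 30%: 0.759; efficiency 0.58.
- p = 20%: 0.700; efficiency 0.49.

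**Step 2: one case by hand.** Power ≈ Φ(atanh(r) × √(n−3) − 1.96), with r = 0.4 and n = 50.
- Continuous: 0.4236 × 6.856 − 1.96 = 0.944; power 83%.
- 50% share: r becomes 0.319; 0.331 × 6.856 − 1.96 = 0.307; power 62%.
- 30% share: r becomes 0.304; power about 57%.

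**Step 3: simulation** (40,000 runs per cell, two-sided 0.05; power in %, continuous → cut, loss in points).

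| n | r | 50% responders | 30% responders |
|---|---|---|---|
| 38 | 0.3 | 45.6 → 30.9 (14.6) | 46.1 → 28.5 (17.6) |
| 38 | 0.4 | 72.2 → 51.3 (20.9) | 72.0 → 46.9 (25.1) |
| 38 | 0.5 | 90.9 → 73.2 (17.7) | 91.2 → 68.0 (23.2) |
| 50 | 0.3 | 57.3 → 39.8 (17.5) | 57.2 → 36.1 (21.1) |
| 50 | 0.4 | 83.6 → 63.8 (19.8) | 83.9 → 59.2 (24.7) |
| 50 | 0.5 | 96.8 → 84.6 (12.2) | 96.8 → 79.9 (16.9) |

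Losses were taken before rounding. They run from 12.2 to 25.1 points; the formula in Step 2 gives 13.9 to 25.3 on the same grid. With r from 0.2 to 0.6 and shares down to 20%, the range is 3.3 to 32.3.

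**Step 4: ranking, which is closer to the planned selection.** With 200 metabolites, 10 of them true predictors at r = 0.3 (3,000 runs), the number of true predictors in the top 10 falls as follows:
- n = 50: from 4.7 to 3.4 (50% share) or 3.1 (30%).
- n = 38: from 3.8 to 2.7 or 2.5.

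The direction was the same at r = 0.2 and with a 20% share.

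A one-component PLS simulation (n = 50, true r = 0.35, 50% share, 600 runs) placed 5.9 of 10 true predictors in the top 10 with the continuous response, against 4.1 with the class label. The AUC for classifying new patients was 0.717 against 0.685. With a 30% share the results were 5.8 against 3.9, and 0.723 against 0.683.

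**Step 5: when the loss disappears.** Suppose response consists of two equal latent classes whose means lie d SDs apart, cut at the midpoint. The efficiency of the cut is then [(2Φ(d/2) − 1) / ((d/2)/√(1 + d²/4))]²: 73% at d = 1, 93% at d = 2 and 108% at d = 3.

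**The case against.** - **The response measure is inferred.** A reader might conclude that the plan demonstrably cuts DAS28 change, perhaps at 0.6. The Metabolomics section names neither. The 0.6 is an expected group difference between diets, not an individual threshold, and a composite or categorical definition is possible. This stands, so the point is conditional on a graded measure. It would apply in the same way to HAQ or a quality-of-life score.
- **A condensed article leaves detail elsewhere.** A fuller plan may define response and could add a regression. But the article does more than omit detail: it fixes both the model and the selection rule on two classes, and supplying a cut-off later would not change that.
- **The stated aim is classification.** A discriminant model is a natural match for predicting responders. However, a graded model with a cut applied to its predictions answers the same question, and in the PLS simulation it classified new patients slightly better. That gain in AUC is small, about 0.03 to 0.04.
- **Power per metabolite is a proxy.** OPLS-DA ranks metabolites jointly and does not test each at a fixed level. This stands; the ranking results support the direction, not the exact number of points.
- **The mechanism is unknown.** The Background suggests that response may depend on genetics or the microbiome, so distinct classes are conceivable, and Step 5 shows the loss could then vanish or reverse. It is therefore not right to say that the loss occurs under any definition of response.

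**Conclusion.** The point holds as a conditional one. The article ties the supervised model and the shortlist to a two-class label and describes no supervised model of graded response. If response is a graded measure such as DAS28 change and relates roughly linearly to the metabolites, the label keeps about 58 to 64% of the information at a 30 to 50% responder share. The proxy power loss is about 12 to 25 points for r = 0.3 to 0.5, n = 38 to 50 and unadjusted two-sided 0.05, and about 3 to 32 points more widely. None of the values for r, share or level comes from the documents, so these figures are scenarios and not properties of the plan.

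A reader might also infer that a null metabolomics result could come from the cut alone. That is not shown: in the PLS simulation the class-label model still found 4.1 of 10 true predictors and reached an AUC of 0.685, which is weaker but not null. The analysis is exploratory, and neither the primary DAS28 comparison nor its sample size is touched.

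**What to change.** In the Metabolomics section, name the continuous response measure and make an OPLS or PLS regression on it the main supervised model, with metabolites selected from that model. If a statement about responders is wanted, apply a pre-stated cut to the cross-validated predictions and report sensitivity, specificity and AUC. Keep the responder/non-responder OPLS-DA as a descriptive companion.

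This takes one or two sentences and uses the same samples, assays and family of methods. The regression is slightly less immediate to read than a two-group plot, which the retained OPLS-DA display offsets. It is also more sensitive to outlying changes, which a check of influential patients would reveal.

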### Strengths

ADIRA trial has several strengths. It has a cross-over design that minimizes individual variation between diet groups. The trial is population-based in that all eligible patients with RA in the region are identified through the Swedish Rheumatology Quality Register and invited to participate. Patients are randomized to a specific diet at the beginning of the study, meaning that effects of season, holidays and carry-over from previous test period should be evenly spread between the two diets. The intervention diets are developed by registered dieticians and have a similar content of macronutrients and energy. The food bags are delivered to participants’ homes by a home delivery food chain every week, which is convenient for participants. Also the meals are easy to prepare or ready meals, with a high nutritional quality. The food bags are referred to as the fiber bag and the protein bag to partially blind participants, and assessors of outcome are fully blinded.

The primary outcome measure, DAS28, is the most clinically relevant outcome and often used in double-blinded pharmacological interventions. The trial is carried out in collaboration with rheumatologists and, hence, results can easily be shared with treating physicians. Compliance to the diet is measured with objective food biomarkers. In addition, metabolomics will be used to identify biomarkers of response to the intervention, and an evaluation of the cost effectiveness of the trial also will be performed.

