Also, participants only receive about 50% of their total dietary intake during 5 days of the week during each 10-wk diet period. They are instructed to add foods in line with the intervention diet, but we cannot fully know to what extent this is happening. Objective biomarkers of compliance are used together with a telephone interview half way through each diet period and a 3-d food record at the end of each diet period. This will only partially capture compliance. However, because ADIRA is a cross-over study each participant acts as his/her control. Likely, the home diet will be similar for each individual in both diet periods except for what is guided by the intervention and this will minimize the effect of the home diet on the intervention. In addition, it is possible that the 10 week long period of each diet may be too short to provide a measurable effect on disease severity. Finally, RA is a disease where activity varies over time and pharmacological treatment changes periodically. This will likely dilute any true effects on disease activity of one diet over the other. Still, evaluations of additional treatment for patients with RA are needed and should be performed while accounting for these methodological challenges.

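### As worded, the responder metabolomics cannot separate metabolites that predict diet response from those that mark patients who would improve anyway

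*Protocol article*

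**What the plan says.** Prediction is a stated aim. Among the specific questions in the Research objective section is "if metabolomics can be used to predict responders". The abstract's Methods paragraph repeats it: "Metabolomics will be used to evaluate the potential to predict responders to dietary treatment". The Strengths section says that "metabolomics will be used to identify biomarkers of response to the intervention".

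The Metabolomics section gives the method. After an unsupervised step (PCA), OPLS-DA and a paired-data variant, OPLS-EP, "will be performed to compare metabolites between patients who respond" and patients who do not. The response is to what the section calls the inflammatory diet (taken here to mean the anti-inflammatory diet). Then "metabolites providing the greatest discrimination between groups of responders vs. non-responders will be identified" with the help of databases. The section does not define response and does not mention the control diet.

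The Limitations section concedes that "RA is a disease where activity varies over time and pharmacological treatment changes periodically". It also relies on the cross-over giving every participant an own control.

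**The concern.** Predicting response to a diet means finding a baseline feature that goes with a larger effect of that diet compared with the alternative. Improvement during one diet period is a different quantity. It also contains whatever the patient's disease would have done anyway, any drug change in those ten weeks, and the return of an unusually high or low starting value towards the patient's usual level. A metabolite linked to any of these will separate improvers from non-improvers even if it has nothing to do with the diet.

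The cross-over supplies what is needed to remove most of this, because each completer also has a control-diet outcome. The contrast as worded does not call on it. At stake is the meaning of any responder biomarker the trial reports: a prognostic marker could be read as a guide to who should be offered the diet.

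**Working it through.** **Inputs from the protocol article (Sample size).** Difference 0.6 DAS28 units, power 90%, α = 0.05, 38 patients needed, 50 included. No SD is given, so 38 cannot be reproduced, only inverted.

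**Implied SD of the within-patient difference.** From n = (SD × (z₀.₉₇₅ + z₀.₉₀) / δ)²:

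SD = 0.6 × √38 / (1.960 + 1.282) = 3.699 / 3.242 = 1.14.

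The t-based version, two-sided, gives 1.11. The per-visit within-patient SD is then 1.11 / √2 = 0.79.

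**Simulation (2,000 runs per row).** Let m be a standardised metabolite and let b and e be within-patient errors at the start and end of a period, each with SD 0.79.

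- Improvement on the intervention diet: b₁ − e_A + trend + θ
- Improvement on the control diet: b₂ − e_C + trend
- Within-patient diet difference (control end minus intervention end): e_C − e_A + θ

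Assumed, not from the article: mean diet effect θ = 0.3; a responder improves by at least 0.6; one metabolite is tested at two-sided 5%; the prognostic trend is the same in both periods (0.4 or 0.6 DAS28 per SD of m); no period or carry-over effect. In the last row of the table, θ has SD 0.6 and correlation 0.7 with m.

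Share of trials in which the metabolite is flagged, n = 50:

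| Metabolite | Responders vs non-responders, intervention diet | Same test, control diet | Diet difference, dichotomised | Diet difference, continuous |
|---|---|---|---|---|
| Unrelated to anything | 4.8% | 4.1% | 5.3% | 5.0% |
| Prognostic, 0.4 | 46.4% | 44.8% | 4.0% | 4.6% |
| Prognostic, 0.6 | 79.1% | 77.1% | 4.2% | 4.4% |
| Correlated 0.3 with the intervention-period baseline flare | 20.9% | 5.2% | 4.8% | 5.2% |
| Correlated 0.5 with that flare | 52.0% | 4.9% | 4.6% | 5.0% |
| True modifier of diet response | 45.4% | 5.1% | 45.9% | 66.2% |

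The simulation standard error is about √(0.05 × 0.95 / 2000) = 0.5 percentage points near 5% and √(0.46 × 0.54 / 2000) = 1.1 points near 46%.

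With n = 38 the pattern is the same. Prognostic metabolites are flagged in 38% and 68% of trials by the one-diet contrast, against about 5% with the continuous difference. The true modifier is found in 38% and 54% respectively.

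**Reading the table.**

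- A prognostic metabolite is flagged almost equally often on either diet, so the one-diet contrast cannot show that it concerns the diet. The same test on the control diet exposes it.
- A metabolite tied to the baseline flare is not exposed by the control-diet run as simulated, but the diet difference removes it.
- The higher power for a true modifier comes from not dichotomising: the one-diet and the dichotomised paired contrasts find it about equally often (45% and 46%).

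**The case against.** The strongest reply is that the article never defines response. The trial's questions are framed against a usual Swedish diet, outcomes are compared between regimens, and a paired-data method is named. Response may therefore be meant relative to control, and a condensed article may leave that definition to the full protocol or analysis plan. This stands in part: the one-diet reading is natural but not certain. Naming OPLS-EP does not settle it. That method pairs metabolite profiles within a patient, while the label that sorts patients still refers to response to one diet. The loss of power from a responder split applies under either reading.

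A reader might also infer three stronger points that the documents do not support.

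- *That the analysis finds fluctuation and prognosis instead of diet response.* A true modifier is still found in about 45% of simulated trials, and an unrelated metabolite is flagged at the nominal rate. The result is a mixture that cannot be separated. The paired difference also keeps random fluctuation, because there is one period per diet.
- *That selecting the best discriminators guarantees spurious separation.* The article does not say that validation will be skipped, and cross-validation and permutation testing are ordinary analysis-plan content. The sentence on greatest discrimination goes on to databases, so it describes chemical annotation at least in part.
- *That the share of patients who pass a cut-off by chance shows the harm.* With SD 1.11 and no diet effect, P(Z > 0.6 / 1.11) = 29%. The same figure applies to a dichotomised paired difference, so it says nothing specific about the one-diet contrast.

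Regression to the mean should not be overstated either. The DAS28 threshold applies at screening and baseline is a later visit, so part of the selection effect has passed before change is measured.

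**Conclusion.** The point holds on the natural reading of the Metabolomics section: the stated contrast does not isolate the diet response that the article says it will predict. Under the assumed effects at n = 50, prognostic metabolites are flagged in 46% to 79% of trials, against 4% to 5% with the within-patient difference. Metabolites tied to the baseline flare are flagged in 21% to 52%, against about 5%. Detection of a true modifier rises from about 45% to 66% when the paired difference is kept continuous. The sizes depend on the back-solved SD, the 0.6 cut-off and the assumed effects. The direction for prognosis does not, provided the prognostic effect is similar in both periods.

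The analysis is exploratory and outside the listed primary and secondary outcomes. This is a worthwhile correction to one stated research question and no threat to the trial's main result. If response was already meant relative to the control diet, a clarifying sentence settles the confounding, and only the advice against dichotomising remains.

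**What to change.** - Define response as each participant's control-minus-intervention difference in end-of-period DAS28, kept continuous.
- Relate it to metabolites measured before the diet. Equivalently, test a metabolite-by-diet interaction in the mixed model, with period as a term. The trial-baseline sample precedes both diets for everyone.
- Run the same analysis on change during the control diet as a negative control. This needs a DAS28 value before each period; the text describes the baseline visit, and the schedule figure was not available to confirm a second one.
- Report the result as hypothesis-generating, and state that with one period per diet random within-patient fluctuation remains in the response.

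The cost is wording and computing on data from completers. Participants with only one period drop out of the paired-difference analysis.
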